#### **2.5.6 Sample Size and Feasibility Analysis:**

Based on the retrospective analysis data of our center, the estimated 3-year progression-free survival (PFS) for patients with FIGO stage IB, IIA, and IIIC cervical cancer following primary treatment was observed to be 65%. This investigation is designed to demonstrate a statistically significant 13% improvement in PFS, corresponding to an anticipated 3-year PFS rate of 65% in the control cohort compared to 78% in the experimental arm. Recruitment is expected to take 2 years, with a 3-year follow-up period. Utilizing a conventional significance level ( $\alpha$ ) of 0.05 and statistical power ( $1 - \beta$ ) of 0.9 ( $\beta = 0.1$ ), with a 5% anticipated attrition rate and 1:1 randomization scheme, sample size calculations determined a requirement of 211 cases per group. This determination was cross-validated through PASS 15, nQuery, and G\*Power statistical software.

Considering substantial variability in PFS rates reported across existing literature,

we implemented a 10% sample size augmentation strategy to enhance detection sensitivity for clinically meaningful differences, mitigate type II error risks, and improve result validity. This adjustment results in a revised minimum enrollment target of 233 participants per group, yielding an anticipated statistical power of approximately 95% for detecting the hypothesized treatment effect.

This study plans to enroll at least 466 patients with cervical cancer who have undergone radical surgery and have full-thickness or outer full-thickness stromal invasion. Fudan University Shanghai Cancer Center treats nearly 1,000 cases of cervical malignancies annually, including approximately 300 cases of radical radiotherapy and 600 cases of postoperative adjuvant radiotherapy. Thus, the hospital has sufficient capacity to complete the required number of cases for this trial. The Gynecological Oncology Department has been conducting intensity-modulated radiation therapy (IMRT) for cervical cancer since 2007 and has completed approximately 4,000 cases of IMRT for cervical cancer, demonstrating technical maturity. Additionally, the hospital's molecular pathology laboratory has mature detection techniques.

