#### 2.5.7.10 Reporting of Results

479 Results will be reported following the CONSORT guidelines for randomized  
480 controlled trials.

481 Both statistical significance and clinical relevance will be considered when  
482 interpreting the findings.

483 All P - values presented are two - sided, and P - values less than 0.05 will be  
484 considered statistically significant.

485 Confidence intervals will be reported at the 95% level for key outcome measures  
486 to quantify the precision of the estimates.

487

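### The stated power of about 95% at 233 per group is modestly overstated: the protocol's own inputs give about 92–93% after its 5% attrition

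*Protocol*

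**What the plan says.** All the figures are in Protocol section 2.5.6 unless another section is named.

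- **Effect:** "corresponding to an anticipated 3-year PFS rate of 65% in the control cohort compared to 78% in the experimental arm".
- **Error rates:** alpha "of 0.05 and statistical power ( $1 - \beta$ ) of 0.9". The section does not state sidedness, but section 2.5.7.10 does for reported results: "All P - values presented are two - sided".
- **Attrition and allocation:** "with a 5% anticipated attrition rate and 1:1 randomization scheme".
- **Timing:** "Recruitment is expected to take 2 years, with a 3-year follow-up period".
- **Result:** "sample size calculations determined a requirement of 211 cases per group".
- **Augmentation:** 10% is added because published PFS rates vary, giving at least 233 per group (466 in total), "yielding an anticipated statistical power of approximately 95% for detecting the hypothesized treatment effect".

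Section 2.5.7.5.2 assigns the log-rank test and Cox regression to time-to-event outcomes. Section 2.5.6 names no test or formula behind 211, and does not say whether the 95% counts patients before or after attrition.

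**The concern.** At a fixed effect and alpha, the expected test statistic grows with the square root of the sample size. Ten per cent more patients raises it by about 5%, which is too little to take power from 90% to 95%. So either 211 per group has more than 90% power, or 233 has less than 95%.

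What is at stake is the accuracy of the type II error. The section gives reducing that error as one reason for the extra patients, yet implies about 5% where its inputs give about 7–8% after attrition. No patient, endpoint or decision rule depends on the figure.

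**Working it through.** **Inputs.** From section 2.5.6: 3-year PFS 65% and 78%, alpha 0.05, power 0.90, 5% attrition, 1:1 allocation, 2 years of recruitment, 3 years of follow-up, 211 and 233 per group. From section 2.5.7.10: two-sided testing. From section 2.5.7.5.2: log-rank. Assumptions: exponential PFS, uniform accrual, and the 3 years counted from the last patient's entry.

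**1. The augmentation.** 211 × 1.10 = 232.1, rounded up to 233. Agrees with the plan.

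**2. Can 211 be reproduced?**
- Yearly hazards: −ln(0.65)/3 = 0.1436 and −ln(0.78)/3 = 0.0828. HR = ln(0.78)/ln(0.65) = 0.577 and ln(HR) = −0.550.
- Event probability per arm: 1 − [exp(−3λ) − exp(−5λ)]/(2λ) = 0.435 and 0.281, mean 0.358.
- Events for 90% power, Schoenfeld: 4 × (1.960 + 1.2816)² / 0.550² ≈ 139.
- Events for 90% power, Freedman: (1.960 + 1.2816)² × [(1 + 0.577)/(1 − 0.577)]² ≈ 146.
- Per group with attrition, events/(2 × 0.358 × 0.95): about 205 (Schoenfeld) and 215 (Freedman). The Lachin–Foulkes formula gives 213.

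The stated 211 lies inside this range, so a log-rank basis with 2 + 3 years is a plausible origin.

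**3. Internal consistency, with no accrual or formula assumption.**
- Power at 233 if 211 gives 90%: Φ[(1.960 + 1.2816) × √(233/211) − 1.960] = Φ(1.446) = 92.6%.
- Increase needed for 95%: [(1.960 + 1.645)/(1.960 + 1.2816)]² = 1.237, and 211 × 1.237 ≈ 261 per group. That is 24% more, not 10%.
- In reverse, if 233 gave 95%, 211 would give Φ[3.605 × √(211/233) − 1.960] = Φ(1.470) = 92.9%.

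**4. Direct log-rank power at 233 per group.** After attrition 466 × 0.95 = 442.7 patients remain, with 442.7 × 0.358 ≈ 158.5 events. Without attrition there are 166.9 events.
- Schoenfeld: Φ(√d × 0.550/2 − 1.960).
- Freedman: Φ(√d × (1 − 0.577)/(1 + 0.577) − 1.960).

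| Method | After 5% attrition | No attrition |
|---|---|---|
| Schoenfeld | 93.4% | 94.5% |
| Lachin–Foulkes | 92.4% | 93.6% |
| Freedman | 92.2% | 93.4% |
| Simulation, 20,000 runs | 92.8% (5% removed outright) or 93.5% (5% lost gradually by 3 years) | 94.3% |

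No entry reaches 95%. All exceed 90%.

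**The case against.** The best defence is that the word approximately covers the gap. Schoenfeld's formula gives 94.5% before attrition, and the section does not say which way attrition is counted. Nor does it report the power achieved at 211. By Schoenfeld, 211 per group has 90.9% after attrition and 92.3% before, so the same formula can run from 92.3% at 211 to 94.5% at 233. This stands in part: the 92.6% and the 261 depend on taking 211 as exactly 90%, and calling the 95% simply wrong would be too strong. But the defence needs the most favourable formula, and it drops the attrition that the same paragraph builds into 211.

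One-sided testing does not rescue the pair either. Scaling from 211 at 90% then gives 92.4%. With 2 + 3 years, a one-sided 0.05 test would have 95.9–96.6% power at 233 after attrition, but would need only about 168–175 per group for 90%, far from 211. It would also conflict with the two-sided rule in section 2.5.7.10.

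A reader might go further in two ways that the document does not support.

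- **Power is really 86–88%, below the 90% target.** That is a two-sided two-proportion test at 3 years (87.7% with 233 evaluable, 86.0% with 221). A log-rank test cut at 3 years per patient gives a similar 85–89%. The two-proportion method needs 252 per group (266 with attrition), so it does not reproduce 211. Sections 2.1 and 2.5.4 define PFS as a time from randomization, section 2.5.7.5.2 assigns the log-rank test to such outcomes, and section 2.5.4 schedules visits beyond 3 years. The lower figures apply only if 3-year PFS were compared as a proportion or follow-up were cut at 3 years.
- **The software cross-validation claim is false.** One method's failure to give 211 does not show this. The procedures run in each package are not stated, and log-rank formulas give about 205 to 215.

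**Conclusion.** The concern holds as a minor point. The stated 95% is too high by about 1.5 to 3 percentage points after the section's own 5% attrition (92.2–93.4% by formula), and by as little as 0.5 points if attrition is ignored and Schoenfeld's formula is used. The implied type II error is about 7–8% rather than 5%.

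This rests on a two-sided 0.05 log-rank test, exponential PFS with HR 0.577, uniform 2-year accrual and 3 years after the last patient. The scaling check needs none of the accrual or distribution assumptions, only that 211 corresponds to 90%. On the planned test with full follow-up, power exceeds the 90% target, so the 466 target remains adequate for the hypothesized effect.

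**What to change.** Keep 466 patients. In section 2.5.6, replace the 95% with a statement such as: power is approximately 92–93% after 5% attrition, for a two-sided 0.05 log-rank test with hazard ratio 0.577, 2-year accrual, 3 years of follow-up after the last patient and about 158 expected PFS events. Name the formula used and say that attrition is already deducted. If the sponsor's own calculation behind 211 rests on a different basis, state that basis and give the power at 233 on it.

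The cost is the rewording of one paragraph. No patients are added, no analysis changes, and the quoted power becomes slightly less favourable.

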### **2.5.7 Statistical Analysis:**

#### **2.5.7.1 Data Management**

All data collected during the trial will be recorded on case report forms (CRFs) and then entered into a secure, password - protected electronic database.

Data will be checked for accuracy and completeness, and any discrepancies or missing data will be queried and resolved in a timely manner.

Regular data monitoring and cleaning procedures will be conducted throughout the study to ensure data quality.

#### **2.5.7.2 Statistical Analysis Plan**

The statistical analysis plan (SAP) will be developed prior to database lock and will specify all analysis methods, including the primary and secondary outcome measures, subgroup analyses, and handling of missing data.

The SAP will be followed strictly during the analysis phase to avoid data - driven

analyses and ensure the integrity of the study results.

#### 2.5.7.3 Analysis Population

The primary analysis will be conducted on the intention - to - treat (ITT) population, which includes all randomly assigned patients, regardless of their actual treatment received or whether they completed the study as planned.

For safety analyses, all patients who received at least one dose of the study treatment will be included in the safety population.

#### 2.5.7.4 Sample Size Calculation and Rationale:

Refer to section 2.5.6.

#### 2.5.7.5 Description of Statistical Methods:

All enrolled patients were randomized into groups using computer-generated allocation.

The primary outcome will be compared between groups.

##### 2.5.7.5.1 Descriptive Statistics

For continuous variables, summary statistics such as mean, standard deviation, median, and interquartile range will be reported.

For categorical variables, frequency counts and percentages will be presented.

Appropriate graphical displays (e.g., histograms, box plots, bar charts) will be used to visualize the distribution of key variables.

##### 2.5.7.5.2 Comparative Analyses

The primary outcome will be compared between groups using independent - samples t - test for continuous variables assuming normal distribution, Mann - Whitney U test for non - normally distributed continuous variables, chi - square test or Fisher's exact test for categorical variables.

For time - to - event outcomes, Kaplan - Meier survival curves will be estimated, and the log - rank test will be used to compare groups. Hazard ratios and their 95%

confidence intervals will also be calculated using Cox proportional hazards regression models.

For secondary outcomes, similar comparative methods will be applied as appropriate for each outcome type.

#### 2.5.7.6 Handling of Missing Data

The amount and pattern of missing data will be assessed for each key outcome variable.

Sensitivity analyses will be conducted to evaluate the potential impact of missing data on the study results.

#### 2.5.7.7 Subgroup Analyses

Specified subgroup analyses will be conducted to explore the treatment effect in different subgroups of patients, including but not limited to SIB or Non-SIB groups, tumor size groups, etc.

These subgroup analyses will be interpreted with caution, considering the potential for multiple comparisons and the exploratory nature of these analyses.

#### 2.5.7.8 Adverse Event Analysis

The incidence and types of adverse events (AEs) will be summarized for each treatment group.

The severity and relatedness of AEs to the study intervention will also be evaluated and reported.

Comparative analyses of safety data between groups will be performed using appropriate statistical methods (chi - square tests for categorical AE data).

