## **II. Research Content and Technical Key Points**

### **2.1 Research Objectives:**

This study aims to evaluate the potential benefits of adjuvant chemoradiotherapy with or without a simultaneous integrated boost in patients with early-stage cervical cancer who have undergone radical surgery and have full-thickness or outer full-thickness stromal invasion.

- **Primary Objective:** 3-year progression-free survival.
- **Secondary Objectives:** 3-year overall survival rate, acute and late toxicities, and progression patterns.

Progression-free survival (PFS): PFS is defined as time from randomization to first radiological/histopathological progression or all-cause death.

Overall survival (OS): Refers to the time period from the date of receiving study treatment to the date of death (any cause). Subjects without an observed death will be censored at the time of confirmed survival.

Acute and late toxicities: KPS score, vital signs, Physical examination, laboratory tests (blood routine examination, routine urine and stool test), comprehensive metabolic panel, coagulation test and so on), ECG, Cardiac ultrasound, adverse events (AEs), AEs is recorded based on CTCAE 5.0 criteria.

Progression patterns: Analyze the progression pathways of the disease, including local-regional recurrence (pelvic region/vaginal cuff/para-aortic nodes), distant metastasis (inguinal nodes, intra-abdominal sites, lungs, liver, bones), tumor bed boost local control (absence of recurrence within the contoured SIB volume)

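### Section 2.5.7.8 names only chi-square for adverse events, which does not suit late toxicity observed for unequal times; if recording ended at progression it would modestly disfavour the boost

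*Protocol*

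**What the plan says.** Section 2.1 lists the secondary objectives as "3-year overall survival rate, acute and late toxicities, and progression patterns". It gives no boundary between acute and late events and no time horizon for late ones.

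Section 2.5.7.8 promises that "The incidence and types of adverse events (AEs) will be summarized for each treatment group". It leaves the comparison between arms to suitable methods, of which it names one: "chi - square tests for categorical AE data". Under 2.5.7.3 the denominator is every patient who had at least one dose.

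On observation time, 2.5.6 states: "Recruitment is expected to take 2 years, with a 3-year follow-up period". Section 2.5.4 schedules three-monthly visits for 2 years and then six-monthly visits for a further 3 years, ending earlier only at death, whether or not treatment was completed. Nothing says that toxicity recording stops at progression, and nothing says that it continues. Section 2.5.5 defines adverse events as those arising in the course of radiotherapy and chemotherapy, which does not fit late toxicity.

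Section 2.5.7.5.2 provides Kaplan-Meier, log-rank and Cox methods for time-to-event outcomes and extends comparable methods to secondary outcomes according to their type.

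**The concern.** Chi-square on the proportion with an event is reasonable for acute toxicity, where nearly everyone is observed for the whole short window. Late toxicity accrues over years. A patient who dies or is lost at 8 months without a late event has shown little about late risk, but enters the table as a full toxicity-free patient. The resulting proportion mixes different lengths of observation.

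The second question is whether observation time could differ by arm. The design expects more progression in Group B. If progression ended toxicity recording, Group B would have less time in which to show late harm, and a boost that works better would look more toxic. The trial tests added radiation dose, so its benefit-risk conclusion sets a PFS gain against exactly this late harm.

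**Working it through.** **Follow-up at analysis.** The protocol gives no late-toxicity rate to reproduce, so I checked the follow-up assumption against the sample size in 2.5.6. Inputs: "3-year PFS rate of 65% in the control cohort compared to 78% in the experimental arm", two-sided alpha 0.05, power 0.90, "with a 5% anticipated attrition rate and 1:1 randomization scheme".

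- HR = ln 0.78 / ln 0.65 = 0.577.
- Uniform 2-year accrual plus 3 years of further follow-up gives 139 events by Schoenfeld (195 per arm, 206 after attrition) and 146 by Freedman (204 per arm, 215 after attrition). The stated 211 lies between.
- Schoenfeld with a fixed 3-year horizon gives 244 per arm (257 after attrition), which does not match.

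The plan's own figure therefore fits staggered follow-up of 3 to 5 years.

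**What a crude proportion estimates.** Assume late toxicity at 5% per year, with no death or loss. The risk is 1 − exp(−0.15) = 13.9% at 3 years and 1 − exp(−0.25) = 22.1% at 5 years. The crude proportion averages 1 − exp(−0.05t) over t from 3 to 5, which is 18.1%. That value depends on the accrual pattern, and death or loss lowers it further. It is not the risk at a time fixed in advance.

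**Case A: recording ends at progression or death (assumed).** Hazards of progression or death:

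- Group B: −ln(0.65)/3 = 0.1436 per year.
- Group A: −ln(0.78)/3 = 0.0828 per year.

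Mean progression-free time is (1 − exp(−λt))/λ:

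| Horizon | B (years) | A (years) | Ratio |
|---|---|---|---|
| 3 years | 2.44 | 2.66 | 1.09 |
| 5 years | 3.57 | 4.09 | 1.15 |
| averaged over 3 to 5 years | 3.03 | 3.40 | 1.12 |

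With the same late-toxicity hazard h in both arms, the crude proportion is h/(h+λ) × [1 − mean of exp(−(h+λ)t) over t from 3 to 5]. For h = 0.05:

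- B: 0.05/0.1936 = 0.2583; the mean exponential is 0.4639; 0.2583 × 0.5361 = 13.8%.
- A: 0.05/0.1328 = 0.3764; the mean exponential is 0.5896; 0.3764 × 0.4104 = 15.5%.

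| Assumed h per year | B | A | Ratio |
|---|---|---|---|
| 3% | 8.6% | 9.6% | 1.12 |
| 5% | 13.8% | 15.5% | 1.12 |
| 10% | 25.4% | 28.2% | 1.11 |

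At 5% per year the gap is 1.6 percentage points, about 4 patients in 233.

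With a fixed horizon and an assumed true late risk of 5% to 40%, counting late events from randomization or from 3 months after it:

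- At 3 years the ratio is 1.08 to 1.10, and chi-square at 233 per arm rejects in 5.4% to 10.4% of trials instead of 5%.
- At 5 years the ratio is 1.13 to 1.16, with rejection in 6.0% to 16.3%.

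A cause-specific comparison under the same assumptions gives a ratio of 1.00 and keeps the 5% error rate.

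**Case B: recording runs to death.** Only a survival difference can now make time at risk differ. The protocol assumes none, so the survival values below are mine.

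| Assumed 3-year OS, B / A | Ratio at 3 years | Ratio at 5 years |
|---|---|---|
| 80% / 80% | 1.00 | 1.00 |
| 85% / 90% | 1.03 | 1.04 to 1.05 |
| 80% / 87% | 1.04 | 1.06 to 1.07 |
| 75% / 85% | 1.06 | 1.10 |

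**The case against.** A reader might infer that the trial's own hypothesis makes time at risk differ by arm, so that the boost is bound to look more toxic than it is. The documents do not support this. The hypothesis concerns PFS, visits continue to 5 years or death, no section stops toxicity recording at progression, and no OS difference is assumed. The 3-to-5-year spread comes from accrual and is equal between randomized arms, and no difference in loss to follow-up is stated. All of this stands, so the arm bias can only be put conditionally.

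It is also fair that 2.5.7.8 ties chi-square to categorical data and leaves room for other methods. Read with the definition in 2.5.5, it might cover on-treatment events only, leaving late toxicity to 2.5.7.5.2 and to a separate SAP. Strictly, then, the protocol does not commit late toxicity to a crude comparison. But the one section written for adverse events names a single method and draws no line between acute and late. Late toxicity therefore either falls under an unsuitable method or has no comparison in that section. This goes beyond detail left to the SAP, because data collection must already provide onset dates and assessments after progression.

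Finally, with complete follow-up a crude proportion does describe the harm that patients experienced. That stands as a reason to report absolute risk, but not to use chi-square as the sole comparison when follow-up is unequal.

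**Conclusion.** The concern holds in a limited form. The only named method ignores time at risk and does not yield late-toxicity risk at a defined time; this is so whether or not the arms differ.

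Bias against the boost is possible but not established. It needs recording that ends at progression (crude ratio about 1.08 to 1.16, or roughly 0.4 to 4 percentage points) or a survival advantage for the boost (1.03 to 1.10 under the values tried). With recording to death and equal survival it is nil.

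These sizes rest on exponential hazards, PFS as planned, late toxicity independent of progression, and toxicity rates and OS values that the protocol does not give. The change is worth making because it is cheap and bears on the benefit-risk conclusion.

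**What to change.** In 2.5.7.8:

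- Keep chi-square for acute toxicity.
- Define the boundary between acute and late events. Compare time to first grade 3 or higher late event by cause-specific log-rank and Cox model, using the methods already in 2.5.7.5.2 and censoring at the last toxicity assessment.
- Report cumulative incidence at 3 years, with death as a competing event, as the descriptive absolute risk. This does not replace the cause-specific comparison, because it keeps any arm difference that comes from survival.

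In 2.5.4 and 2.5.5:

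- State that late toxicity is recorded at the planned visits regardless of progression, and bring the adverse event definition into line with that.
- Add a sensitivity analysis that censors at the start of salvage treatment.

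The cost is a few sentences, some analysis work and an onset date for each late event, which is hard to recover afterwards. The downside is that events after progression may reflect salvage treatment. If progression is more common in Group B, that would push the comparison the other way, which is why the sensitivity analysis is needed.

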#### 2.5.7.9 Statistical Software

All statistical analyses will be performed using SPSS 19.

#### 2.5.7.10 Reporting of Results

479 Results will be reported following the CONSORT guidelines for randomized  
480 controlled trials.

481 Both statistical significance and clinical relevance will be considered when  
482 interpreting the findings.

483 All P - values presented are two - sided, and P - values less than 0.05 will be  
484 considered statistically significant.

485 Confidence intervals will be reported at the 95% level for key outcome measures  
486 to quantify the precision of the estimates.

487

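### The reporting rule calls every two-sided P-value below 0.05 statistically significant, and nothing marks secondary results as nominal if PFS is negative

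*Protocol*

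**What the plan says.** Section 2.5.7.10 gives the decision rule: every P-value shown is two-sided, and P-"values less than 0.05 will be" considered statistically significant. It makes no exception by type of outcome. The same section asks for clinical relevance to be weighed, for 95% confidence intervals on key outcomes and for CONSORT reporting.

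Section 2.1 names one primary objective, "3-year progression-free survival". The secondary objectives are "3-year overall survival rate, acute and late toxicities, and progression patterns". Progression patterns are then divided into local-regional recurrence, distant metastasis and "tumor bed boost local control (absence of recurrence within the contoured SIB volume"). The secondaries have no order, no exploratory label and no link to the PFS result.

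Section 2.5.7.5.2 says: "For secondary outcomes, similar comparative methods will be applied as appropriate for each outcome type". Section 2.5.7.8 adds between-group comparisons of adverse events, with chi-square tests for categorical data.

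The one multiplicity caveat is in section 2.5.7.7: "These subgroup analyses will be interpreted with caution, considering the potential for multiple comparisons and the exploratory nature of these analyses". It concerns subgroups only.

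Section 2.5.7.2 leaves the detailed methods, including those for secondary outcomes, to a SAP that was not available for this review.

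**The concern.** The protocol is not silent here. It states when a result counts as significant, and the statement covers every P-value. Read with the plan to test the secondaries between arms, it allows a secondary to be declared significant at the full 0.05 whatever happens to PFS.

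What is at stake is the report of a trial whose primary result is negative. The boost is aimed at the tumor bed, and local-regional, distant and tumor-bed recurrence are overlapping parts of the same PFS events. If PFS missed its threshold but one recurrence site, or overall survival, came in below 0.05, the protocol's own wording would support calling that statistically significant. Section 2.5.7.7 shows that the authors saw the issue for subgroups, but the same caution was not extended to the secondaries.

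**Working it through.** **1. The plan's own use of 0.05.** Section 2.5.6 takes alpha "of 0.05 and statistical power" of 0.9, with 3-year PFS of 65% against 78%, 2 years of recruitment, 3 years of follow-up and 5% attrition.

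- HR = ln(0.78)/ln(0.65) = 0.577.
- Schoenfeld events at two-sided 0.05: 4 × (1.960 + 1.282)² / (ln 0.577)² ≈ 139. Under exponential PFS this gives 195 per group, or 206 after dividing by 0.95.
- Freedman: 146 events, 204 per group, 215 after attrition.
- The stated 211 lies between the two. Adding 10% gives 211 × 1.10 = 232.1, stated as 233. Power at 233 per group is 94.5%, or 93.4% with 5% of events lost, against the stated figure of about 95%.

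Section 2.5.6 does not state sidedness, but its figures are consistent with one two-sided 0.05 test of PFS. No alpha is allocated to any other outcome, and no family-wise rate is stated.

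**2. How many secondary tests.** Section 2.1 lists three items: overall survival, toxicities and progression patterns. Splitting toxicity into acute and late gives four. Splitting progression patterns into their three components as well gives six: overall survival, acute toxicity, late toxicity, local-regional, distant and tumor bed. The protocol does not say how many will be tested, so I take k = 3 to 6.

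**3. Chance of at least one false secondary result, all secondary nulls true.** For independent tests this is 1 − 0.95^k. For correlated tests I took k normal test statistics with a common correlation, each tested at two-sided 0.05. The correlations are assumptions.

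| k | correlation 0 | 0.5 | 0.8 |
|---|---|---|---|
| 3 | 14.3% | 12.5% | 9.8% |
| 4 | 18.5% | 15.6% | 11.4% |
| 5 | 22.6% | 18.3% | 12.7% |
| 6 | 26.5% | 20.7% | 13.9% |

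The span is roughly 10-27%. These figures count false results in either direction.

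**4. The scenario that matters: PFS negative and a false efficacy secondary.** Take overall survival plus the three progression-pattern tests, and treat PFS as a fifth null test with the same correlation. Then

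P(at least one of the four significant, PFS not) = P(at least one of the five significant) − P(PFS significant) = P(at least one of five) − 0.05.

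- Correlation 0: 22.6% − 5% = 17.6%.
- Correlation 0.5: 18.3% − 5% = 13.3%.
- Correlation 0.8: 12.7% − 5% = 7.7%.

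The span is roughly 8-18%.

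**The case against.** The strongest objection is that testing order, alpha allocation and the labelling of secondaries are normal SAP content, and section 2.5.7.2 defers to a SAP. That stands as far as it goes: the lack of a hierarchy in the protocol is not in itself an error. It does not dispose of the point, because section 2.5.7.10 fixes a rule for all P-values. A SAP that made the secondaries nominal would have to depart from that sentence, and a SAP that followed it would keep the problem.

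It can also be said that weighing clinical relevance and giving confidence intervals soften the rule. They help interpretation, but they do not change what may be called significant.

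Three stronger readings are tempting, and the documents do not support them.

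- A reader might infer that the protocol promises 5% across the secondaries and delivers about 20%. It promises no such thing: its 0.05 is a threshold for each P-value. Any single figure also rests on an assumed test count and correlation. Equal correlation is itself a simplification, since tumor-bed recurrence lies largely within local-regional recurrence.
- A reader might infer that the trial's main conclusion is at risk. There is one primary endpoint, and its test keeps its 0.05.
- A reader might extend the calculation to a long list of adverse event terms. Section 2.5.7.8 fixes no number of terms, so such a figure would be invented. A false positive on toxicity is also a spurious safety signal rather than a false claim of benefit.

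**Conclusion.** The point holds as a minor one. Section 2.5.7.10 states an unqualified significance rule, the multiplicity caveat reaches subgroups only, and the family-wise rate for the secondaries is therefore uncontrolled. Both ranges in the working depend on the assumed number of tests and common correlation. The first also needs every secondary null to be true; the second needs the PFS null and the four efficacy nulls to be true. They show the order of magnitude and are not properties of the plan. Within those assumptions, every value in both ranges exceeds the 0.05 used for each comparison. The PFS inference and the sample size are untouched.

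**What to change.** Reword the sentence in section 2.5.7.10 along these lines: *The two-sided 0.05 threshold for statistical significance applies to the primary comparison of PFS. P-values for secondary outcomes are nominal and are reported with effect estimates and 95% confidence intervals; no confirmatory claim rests on them. Safety differences are reported in full whatever the PFS result.*

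If the sponsor wants a formal claim on overall survival, one option is to test it at two-sided 0.05 only when PFS is significant. Other controlled schemes would also serve. The SAP should carry the same wording before database lock.

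The cost is a few sentences, with no extra patients or procedures. The downside is that a secondary result below 0.05 could not be claimed as confirmed when PFS is negative.
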